## Introduction

1

The incidence rate and mortality rate of colorectal cancer in China are increasing year by year. Affected by diet and environment, the number of patients with rectal cancer has been high in China so that a large number of surgical treatments in hospital every year. Besides, the disease is also the main cause of death and a major public health problem as the number of patients is the second only to lung cancer and gastric cancer in China. It was estimated that 191,000 people died in 2015.^[1,2]^

With the improvement of living standard, the proportion of the elderly over 65 years old is increasing. Gastrointestinal cancer is the most common malignant tumor in the elderly over 75 years old in China, according to statistics, the annual incidence of colorectal cancer in the elderly over 75 years old in China is about 78,200. At the same time, with the progress of anesthesia technology, the number of elderly people who can receive surgical treatment has increased significantly.^[3,4]^ However, elderly patients with colorectal cancer after surgery are more likely to have adverse postoperative consequences, such as longer hospital stay, the occurrence of various complications, high readmission rate, etc, and the economic costs will be correspondingly high.^[5,6]^ Consequently, we present this research to prove the use of enhanced post-operative recovery (ERAS) which could reduce the adverse consequences of elderly patients after surgery, and improve the rehabilitation effect compared with routine care.

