The surgical team has developed and implemented multidisciplinary care programs, included ERAS, which improves patient outcomes and reduces hospital stay.^[6,7]^ ERAS includes evidence-based changes in traditional care, such as consultation before admission, avoiding mechanical bowel preparation, shortening fasting, carbohydrate drinks for 2 hours before surgery, avoiding fluid overload, minimally invasive surgery, avoiding early removal of drainage tubes, and catheters, and multimodality of opioid retention analgesia, early feeding and activities. In 1 meta-analysis, ERAS during colorectal surgery was significantly associated with the reduction of postoperative complications, total hospital costs, and early recovery of gastrointestinal function, without increasing 30 day readmission or mortality.^[8]^ Another study showed satisfactory short-term clinical results and demonstrated that laparoscopic D2 lymphadenectomy combined with era is safe and feasible.^[7]^ ERAS is widely accepted to be the gold standard for the treatment of colorectal disease in patients.^[8,9]^ However, there are few articles on the elderly. Our study intends to analyze the effectiveness and safety of clinical application of ERAS in elderly patients with colorectal cancer, and to observe its impact on postoperative recovery of elderly patients with colorectal cancer.

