### Intervention

2.3

The case group will receive ERAS:

a.the first guidance: to explain the disease knowledge of patients, simply understand the stoma care methods, without detailed guidance of stoma care methods;b.preoperative preparation: no intestinal preparation was needed;c.intraoperative intervention: the abdominal cavity was washed with warm water to avoid hypothermiad.follow up guidance: the intervention staff only need to conduct telephone follow-up 1 month after discharge to understand the status of patients.

The control group will receive routine treatment and nursing.

a.First guidance: nurses face the patients on admission, one-to-one through oral and written guidanceThe patients understood the disease-related knowledge, stoma nursing methods, and matters needing attention in daily life;b.Preoperative preparation: according to clinical routine operation, assist patients to improve intestinal preparation;c.Intraoperative intervention: according to the traditional process, there is no need for heating intervention and other measures;d.follow up guidance: the intervention personnel kept in touch with the research subjects during the trial, and 1 month after discharge. Telephone follow-up was conducted to understand the nursing ability and quality of life of patients.

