### Data collection

2.4

We will collect the relevant indicators based on the final outcomes. The research assistant will collect the following data:

Basic information:

Age, gender, education level, body mass index, pathological type, and stage of cancer, ASA score of anesthesia, preoperative albumin, and globulin level.

Stress response indicators: Fasting blood glucose, C-reactive protein (CRP)

Immune function index: T lymphocyte subsets (CD3 +, CD4 +, CD8 +, CD4 + / CD8 +) and immunoglobulin (IgG, IgM, IGA)

Psychological assessment: Zung's self-rating Anxiety Scale (SAS) was used to evaluate the anxiety of the 2 groups

Postoperative recovery index and Economics: Anal exhaust time, first fluid intake time, total hospitalization time, total hospitalization expenses, gastric tube indwelling time and urinary catheter indwelling time

Postoperative complications: Anastomotic leakage, intestinal obstruction, pulmonary infection, urinary tract infection, urinary retention, wound infection.

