### Laboratory analyses

2.5

The preoperative values of laboratory tests (BUN, CREA for renal function; AST, ALT for liver function, CRP, CK, CK MB, BNP for Cardiac function; HB, WBC, PLT, PaO2/FiO2, and PaCO2 for blood routine) in the last 7 days before operation were analyzed as baseline values (preoperative). Extra blood samples will be collected on day 1 after surgery for laboratory evaluation. Postoperative complications were evaluated by a doctor certified by an independent committee. In this trial, he will be guided on the diagnostic criteria for specific postoperative complications. The specialist will evaluate all participants until 30 days after surgery.

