### Postoperative complications

2.6

A medical specialist, the outcome assessor, will be instructed about diagnostic criteria in this study for specific postoperative complications. All participants will be evaluated by the outcome assessor until 30 days after surgery. And we will use evidence-based process of comprehensive geriatric assessment (CGA)^[11]^ to evaluate an older patient's general condition and the risk of adverse outcomes

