### Study outcomes

2.7

The degree of pain relief, the length of the first exhaustion, the time of the first meal, the length of hospitalization, and the incidence of complications would report.

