## Discussion

3

ERAS is a process of improving the condition of surgical patients based on evidence-based nursing. The implementation of strengthening postoperative recovery can greatly improve the clinical effect and reduce the cost, making eras an important standard of surgical value-based nursing.^[13]^ An article summarizes the ERAS results of elderly patients (≥65 years) after colorectal surgery. The median overall incidence rate is 23.5%, the median postoperative loss is 6 days, and the overall postoperative complication rate quite high. Conducting this review shows that it is challenging to compare postoperative complications between studies, and the exclusion criteria are different, because there is no uniform way to define or evaluate complications. Many studies only evaluate selected complications or range of complications by organ system. Patients receiving ERAS require lower upfront costs than traditional caregivers. However, the evaluation results of this study should be based on the long-term results and functional results of patient treatment, so the overall cost-effectiveness has not been fully determined, and longer follow-up data is required for further research. This review compare ERAS with routine care, in which primary outcomes including the degree of pain relief, the length of the first exhaustion, the time of the first meal, Length of stay, and the incidence of complications would report. In this study, we want to evaluate the clinical effect of ERAS and traditional care in elderly patients with colorectal cancer surgery through retrospective analysis of the results and risk factors for postoperative complications.

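### Hospital stay and expenses have no stated time window and readmission is not recorded, so return stays may be missed although complications are followed to day 30

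*Protocol article*

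**What the plan says.** Under postoperative recovery and economics, section 2.4 (Data collection) names "total hospitalization time, total hospitalization expenses". The neighbouring items are bowel and feeding milestones and the duration of the gastric tube and urinary catheter. No start, end or readmission rule is given.

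Section 2.7 (Study outcomes) lists stay together with complications: "the length of hospitalization, and the incidence of complications would report". It gives no window for stay, and expenses are not on that list.

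Complications do have a window, stated twice. Section 2.5 (Laboratory analyses) says "The specialist will evaluate all participants until 30 days after surgery", and section 2.6 (Postoperative complications) says "All participants will be evaluated by the outcome assessor until 30 days after surgery".

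The Introduction puts readmission among the problems of elderly patients after this surgery and links it to cost: "high readmission rate, etc, and the economic costs will be correspondingly high". It also cites a meta-analysis of ERAS in colorectal surgery that found fewer complications and lower hospital costs "without increasing 30 day readmission or mortality". Readmission appears in neither section 2.4 nor section 2.7.

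The Discussion reports from the literature that "Patients receiving ERAS require lower upfront costs than traditional caregivers", and adds that overall cost-effectiveness is still unsettled and needs longer follow-up.

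**The concern.** Discharge ends the index admission, and its timing is something the intervention is expected to change. If hospital days and expenses are counted only up to discharge, each patient's observation period is set by an outcome, while complications are observed over a fixed period.

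Suppose a patient in each group develops the same complication on day 7. If the control patient is still in hospital, the extra days and expenses are captured. If the ERAS patient went home on day 6 and has to return, they are not. The two patients count equally for complications but unequally for stay and cost.

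At stake is the interpretation of a shorter stay or a lower bill. With no record of readmission, the trial could not tell a real saving from one partly offset by return stays. Nor could it show the opposite: if ERAS reduced readmissions, index-only figures would understate its benefit.

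**Working it through.** The article gives no figure for cost, bed-days or readmission in this trial, so there is none to reproduce. The check has two parts.

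**1. The sections side by side**

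| Item | Window stated | Return stays |
|---|---|---|
| Hospital time and expenses (2.4) | none | not addressed |
| Length of stay (2.7) | none | not addressed |
| Complications (2.5, 2.6) | to 30 days after surgery | not applicable |
| Readmission (Introduction) | part of the rationale | not in 2.4 or 2.7 |

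No section says that time and expenses stop at the first discharge. That reading is an inference. It rests on the neighbouring items, which are all events of the first stay, and on the absence of any item that would capture a return.

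**2. Size of the effect if the figures are index-only**

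Let p be the proportion of patients readmitted and L the mean length of a return stay, taken as equal in the two groups. Then:

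unseen difference in days per patient = (p in ERAS − p in control) × L

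All inputs are assumptions: L from 3 to 10 days, and a difference in p from 0 to 10 percentage points.

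| Difference in p | L = 3 | L = 5 | L = 7 | L = 10 |
|---|---|---|---|---|
| 0 | 0 | 0 | 0 | 0 |
| 2 points | 0.06 | 0.10 | 0.14 | 0.20 |
| 5 points | 0.15 | 0.25 | 0.35 | 0.50 |
| 10 points | 0.30 | 0.50 | 0.70 | 1.00 |

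For example, 0.05 × 7 = 0.35 day and 0.10 × 10 = 1.00 day per patient.

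The sign follows the difference. If readmission is higher under ERAS, index-only figures flatter ERAS by these amounts. If it is lower, they understate the ERAS advantage by the same amounts.

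To cancel a 1-day saving in index stay completely, readmission under ERAS would have to exceed control by 1/L:

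- 1/5 = 20 points for 5-day returns
- 1/7 = 14.3 points for 7-day returns
- 1/10 = 10 points for 10-day returns

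Partial offset is therefore plausible, while full reversal needs a large difference. Expenses follow the same pattern if a day of a return stay costs about the same as a day of the index stay, which is a further assumption. The figure of 6 days in the Discussion is not used as a denominator, because its wording is unclear and it describes other studies.

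**The case against.** A reader might infer that the plan stops counting at the first discharge and is therefore biased towards whichever group leaves earlier. The documents do not support either step. The article's *total* could include return stays. Earlier discharge by itself hides nothing: distortion needs a difference in hospital use after discharge. The only evidence cited on this, in the Introduction, is a meta-analysis with no increase in 30-day readmission, and with equal readmission and equal return stays the distortion is zero. These objections stand. They remove any claim of a known direction or size.

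Three further objections carry weight:

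- Expenses are a collected item. They are absent from Study outcomes and from the primary outcomes named in the Discussion, which already concedes that cost-effectiveness is open. This lowers the stake for cost, though length of stay is on both lists.
- Recovery milestones naturally end when they are reached, so a window that differs from the one for complications is not in itself an error.
- This is a condensed article, and a full protocol may define the terms.

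The last objection does not dispose of the point. The article itemises its data and fixes a window for complications, yet leaves out the one item that its own rationale ties to cost. The reassuring meta-analysis does not settle the matter for this population either, since the Introduction says that little has been published on elderly patients. As listed, the trial would collect nothing with which to check it.

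**Conclusion.** The point holds as a minor one. Hospital time and expenses have no stated window, and readmission is not recorded, although the rationale depends on it and complications are followed to day 30.

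If the measures cover the index admission only, the comparison of stay and cost is distorted whenever hospital use after discharge differs between the groups, in either direction. The amount is zero if use is equal, and up to about 1 day per patient for differences of up to 10 points with return stays of up to 10 days. Those inputs are assumed, and nothing in the article indicates which values within the range will apply. If *total* was meant to include return stays, the remaining defect is only that the article does not say so.

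**What to change.** Record every readmission to day 30 after surgery. Keep the index-admission figures, label them as such, and report beside them all hospital days and hospital expenses from admission to day 30 after surgery, including return stays. Start the count at admission and not at surgery, because preoperative preparation differs between the groups (section 2.3) and its days and expenses belong in the comparison.

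Take the data from the hospital's own billing records, in the same way for both groups. The existing telephone contact cannot be the main source. In the ERAS group it is a single "telephone follow-up 1 month after discharge to understand the status of patients", while control patients are also contacted during the trial. The call is also timed from discharge and not from surgery. Care received elsewhere should be asked about with the same question at the same time in both groups, and treated as supplementary.

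The cost is a billing extract for at most 110 patients (the number in section 2.11) and one added question. The downsides are that any saving may look less favourable than on index figures alone, and that care elsewhere is only patient-reported.

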**Results::**

This study will help to evaluate the clinical feasibility, safety and effectiveness of ERAS in elderly patients undergoing colorectal resection compared with routine care.

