### Patient population and eligibility criteria

2.2

Inclusion criteria:

(1)all meet the relevant diagnostic criteria for colorectal cancer;(2)all confirmed by electronic colonoscopy and pathological examination;(3)age ≥ 65 years old;(4)consciousness and mental state are normal;(5)operations are all laparoscopic, and all meet the indications of laparoscopic surgery;

Exclusion criteria:

(1)patients with mental disorders such as severe cognitive impairment;(2)patients with severe organ diseases who cannot perform laparoscopic surgery;(3)patients with intestinal obstruction and unable to withstand surgery;

Flow chart is shown in Figure 2.

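### Safety is a stated aim, but the listed complication data are six selected types, and neither the listed data nor the outcomes include mortality

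*Protocol article*

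**What the plan says.** The Abstract (Results) states the aim: "This study will help to evaluate the clinical feasibility, safety and effectiveness of ERAS in elderly patients undergoing colorectal resection compared with routine care". The Introduction repeats effectiveness and safety as the purpose. Eligibility (section 2.2) sets "age ≥ 65 years old".

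Section 2.4 (Data collection) names the complications: "Postoperative complications: Anastomotic leakage, intestinal obstruction, pulmonary infection, urinary tract infection, urinary retention, wound infection". These are two bowel events, one pulmonary, two urinary and one wound event. The recovery and economic items in the same section are "Anal exhaust time, first fluid intake time, total hospitalization time, total hospitalization expenses, gastric tube indwelling time and urinary catheter indwelling time".

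Section 2.7 (Study outcomes) names pain relief, first exhaust, first meal and, to close the list, "the length of hospitalization, and the incidence of complications would report". The Discussion repeats these five and calls them primary.

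Sections 2.5 and 2.6 have an outcome assessor, instructed on criteria for specific complications, follow every participant to day 30 after surgery. Section 2.8 (Adverse events) describes patients who died after cancer resection in general and sets no collection of deaths in this trial. Section 2.9 makes an unacceptable risk of serious adverse events a ground for ending the trial, and section 2.12 sets up an independent team to look at safety data.

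**The concern.** A safety aim in patients of this age needs, at the least, deaths and any serious complication compared between the groups. The listed data offer six types. Death, reoperation, and cardiac, renal, thromboembolic and delirium events are not named in sections 2.4, 2.6 or 2.7.

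The article also argues against its own choice. The Discussion says of earlier research: "Many studies only evaluate selected complications or range of complications by organ system". The Introduction counts the absence of an increase in 30-day readmission or mortality among the evidence for ERAS, and this trial lists neither.

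What is at stake is mainly the missing safety event. If one group had more deaths or more events of unlisted types, the reported comparison would not show it. An analysis plan written later cannot recover events that were never recorded. A second, smaller matter is that length of stay has no stated rule for patients who die in hospital.

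**Working it through.** No figure in the article tests this point directly, so the check has two parts.

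**1. Passages side by side**

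| Place | What it contributes | Mortality named as data or outcome? |
|---|---|---|
| Abstract; Introduction | Safety is an aim | No (mortality appears only in cited evidence) |
| 2.4 Data collection | Six complication types, no open-ended term | No |
| 2.5, 2.6 | Assessor follows to day 30 for specific complications | No |
| 2.7; Discussion | Five outcomes | No |
| 2.8 Adverse events | Deaths as general background | No |
| 2.9, 2.12 | Serious events and safety data, for oversight | No content defined |

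No section turns safety into a between-group outcome beyond the incidence of complications.

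**2. Size, with assumed inputs**

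Denominators: section 2.11 gives 110 patients (55 per group) after a 10% increase, and 110 / 1.10 = 100, so that step is consistent. The base of 100 cannot be derived, because no power, effect size, standard deviation or rate is stated. The Abstract gives 60 patients (30 per group if split equally), so both sizes are shown.

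*Chance of at least one death*, 1 − (1 − p)^n, where p is an assumed 30-day mortality:

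| p (assumed) | n = 110 | n = 60 |
|---|---|---|
| 1% | 67% | 45% |
| 2% | 89% | 70% |
| 5% | 99.6% | 95% |

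*Event rate in one group* if k deaths from unlisted causes were counted, k / n: 1, 2 or 3 deaths among 55 add 1.8, 3.6 or 5.5 percentage points. Among 30 they add 3.3, 6.7 or 10.0.

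*Mean stay* if a day-2 death were entered as a 2-day stay. The assumed typical stay is 6 days, reading the 6-day median in the Discussion as length of stay. The shift is k × (6 − 2) / n. For 1, 2 or 3 deaths the mean falls by 0.07, 0.15 or 0.22 days (n = 55), or 0.13, 0.27 or 0.40 days (n = 30).

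*Complications of unlisted types.* The Discussion quotes a median rate of 23.5% without making clear of what. If it is read as a complication rate, 55 × 0.235 = 12.9 patients per group. If 20% to 50% of these had only unlisted types (assumption), 12.9 × 0.20 = 2.6 to 12.9 × 0.50 = 6.5 patients per group would count as free of complications.

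**The case against.** The strongest reply is that section 2.4 is not a full inventory. Pain relief is an outcome but is missing from it, as are most of the laboratory values of section 2.5 and the geriatric assessment of section 2.6. The section never says that only these six are recorded, and the assessor's specific complications are never equated with them. Sections 2.9 and 2.12 imply that some safety data reach oversight, and adverse-event forms are commonly left to the full protocol. This shows that deaths may well be known to the trial team. It does not make mortality or any wider safety measure an outcome to be compared, and the article does state its outcomes.

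Several stronger readings are tempting but unsupported:

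- A reader might infer that an early death scores as the best result on both stay and complications. The listed variables permit that, but no section says it. Such a patient could be treated as a dropout, or a rule could sit in an analysis plan that is not shown.
- A reader might infer that the trial's complication rate will be set against the literature rate. The planned comparison is ERAS with routine care, and the literature rate is background.
- A reader might infer that cardiac and renal markers are measured on day 1 while no such event is counted. Section 2.5 gives the panel ("BUN, CREA for renal function; AST, ALT for liver function, CRP, CK, CK MB, BNP for Cardiac function") as preoperative baseline values and names no panel for the day-1 samples.
- A reader might infer that length of stay is already compared by a rank-sum test. Section 2.11 keeps that test for rank data and assigns repeated-measures ANOVA to quantitative data.

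It is also fair that the six listed types include genuine safety events, such as anastomotic leakage and pulmonary infection.

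**Conclusion.** The concern holds in a limited form and is a should-fix. Safety is an aim. The complications listed are six selected types, mortality is in neither the listed data nor the outcomes, and the Discussion criticises this kind of selective counting. The references to serious adverse events and safety data define no between-group safety outcome.

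The main consequence is an incomplete safety comparison. On assumed 30-day mortality of 1% to 5%, at least one death is more likely than not at 110 patients throughout the range, and at 60 patients from 2% upwards. The possible distortion of mean stay is minor, and whether it would arise at all is not settled by the document. All sizes rest on assumed mortality, an assumed 6-day stay and an assumed share of unlisted complications; none is a figure the article gives for this trial.

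A reader might go further and ask that safety be dropped from the aims. That would be out of proportion, because the listed events bear on safety and the gap can be closed cheaply.

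**What to change.** - Define the complication outcome as any postoperative complication up to day 30, judged by the existing outcome assessor, with the six listed types reported as components.
- Add 30-day all-cause death and reoperation as safety outcomes, compared between groups.
- State that in-hospital deaths do not enter the length-of-stay comparison as days lived. One option is to give them the worst rank in a rank-based test. This would change the analysis in section 2.11 and should be written as such.

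Cost: a few more fields on the form, with no extra staff or visits, because every patient is already followed to day 30. The stated complication rate will be higher in both groups, and the test for length of stay changes if the worst-rank option is chosen.
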